## Abstract

**Background:**

Hemiplegia is a common sequela after stroke, and acupuncture is one of the most common physical therapies used to treat hemiplegia during the recovery stage after ischaemic stroke. ‘Hand and foot acupuncture with twelve needles’ is an acupuncture treatment performed after stroke. The principal objective of this study is to assess the efficacy and safety of ‘hand and foot acupuncture with twelve needles’ for hemiplegia in the convalescent stage of ischaemic stroke.

**Methods:**

This is the protocol for a randomised, controlled clinical trial with two groups: a ‘hand and foot acupuncture with twelve needles’ group and a routine acupuncture group. A total of 208 participants will be randomly assigned to two different groups in a 1:1 ratio and will undergo conventional rehabilitation. Limb function will be evaluated by the simplified Fugl-Meyer assessment scale, Barthel Index, modified Ashworth scale and National Institute of Health stroke scale. The participants will be evaluated at baseline (on the day of enrolment) and followed up at 2 weeks, 1 month, 2 months and 3 months after enrolment.

**Discussion:**

The results of this study will provide evidence on the effectiveness of ‘hand and foot acupuncture with twelve needles’ in the treatment of limb dysfunction that can be used for future evaluations.

**Trial registration:**

Chictr.org.cnChiCTR1900021774. Registered on 8 March 2019

## Administrative information

The order of the items has been modified to group similar items (see http://www.equator-network.org/reporting-guidelines/spirit-2013-statement-defining-standard-protocol-items-for-clinical-trials/).

## Introduction

### Background and rationale {6a}

In recent years, the incidence of stroke and the associated mortality rate in China have increased [1]. Epidemiological findings show that the age-standardised prevalence, incidence and mortality rates were 1114.8 per 100,000, 246.8 per 100,000 and 114.8 per 100,000, respectively, in 2013 [2]. Ischaemic stroke accounts for 69.6–77.8% of all strokes [2]. China ranks first amongst all countries in terms of the DALYs (disability-adjusted life years) resulting from stroke [1]. Stroke has become the most common and major cause of disability [3, 4]. Approximately 70–80% of the existing stroke patients have lost, to some extent, their ability to work [5]. Hemiplegia, one of the most common sequelae after stroke, directly affects the quality of work and life of patients and imposes a heavy economic burden on society and families [6].

Evidence-based medicine (EBM) has confirmed that rehabilitation training is the most effective treatment for decreasing the disability rate [7, 8]. In modern medicine, the conventional treatments also include exercise therapy [9], traditional Chinese medicine (TCM) exercise therapy [10, 11], medicine [12], acupuncture [12, 13], transcranial magnetic stimulation (TMS) [14–16], mirror therapy [17] and music-supported therapy [18]. In China, acupuncture is one of the most common physical therapies performed to treat stroke-associated hemiplegia and can reduce muscle tension in patients with spastic hemiplegia after stroke [19, 20]. Acupuncture is known to yield better results when the intervention is implemented earlier [21]. However, due to the complexity of patients’ conditions, the processes for selecting safe and effective acupuncture points as well as performing manipulation according to the actual patient conditions need to be explored further.

‘Hand and foot acupuncture with twelve needles’ has been widely used to treat various diseases, such as multiple sclerosis [22] and insomnia [23] and is commonly used for stroke patients. In clinical practice, ‘hand and foot acupuncture with twelve needles’ is often used to treat apoplexy [24]; however, studies such as clinical trials supporting this contention are relatively scarce. Some studies have shown that ‘hand and foot acupuncture with twelve needles’ can effectively reduce the lesion excitability of the contralateral primary motor cortex and improve the excitability imbalance in the bilateral cortex in patients with ischaemic stroke, and there is a significant correlation between the decline in excitability in the cortex and clinical efficacy [25]. Therefore, we designed a clinical trial to observe the primary effects of ‘hand and foot acupuncture with twelve needles’ on stroke hemiplegia.

### Objectives {7}

The objective of this study is to compare the effectiveness of ‘hand and foot acupuncture with twelve needles’ with that of routine acupuncture technique in hemiplegia patients with ‘qi deficiency and blood stasis’ syndrome in the convalescent stage of ischaemic stroke. This study also aims to assess the difference in the effects of these two techniques on motor function, independence in activities of daily living (ADLs), limb spasticity and neurological deficits.

### Trial design {8}

This is an open-label, single-centre, parallel design, 2-arm (allocation ratio 1:1), superiority, randomised controlled trial. A flow diagram of this study protocol is shown in Fig. 1, and the treatment and outcome measures are presented in Fig. 2.

**Fig. 1 Fig1:**
[figure not shown]
Trial flow chart

**Fig. 2 Fig2:**
[figure not shown]
SPIRIT figure

## Methods: participants, interventions and outcomes

### Study setting {9}

Stroke patients with hemiplegia will be recruited from a rehabilitation clinic or ward of Shunyi Hospital, Beijing Traditional Chinese Medicine Hospital in Beijing, China.

### Eligibility criteria {10}

#### Inclusion criteria

Patients satisfying the following six conditions will be included:
A.Diagnosis of ‘apoplexy’ according to TCM and cerebral infarction confirmed by computed tomography or magnetic resonance imagingB.Age of 35 to 80 yearsC.A duration from stroke onset of 2 weeks to 3 monthsD.National Institute of Health stroke scale (NIHSS) score of 5–22E.A limb strength score below grade 4 and limb dysfunctionF.Qi deficiency syndrome and blood stasis syndrome confirmed by the ‘Ischemic Ischaemic Stroke TCM Syndrome Diagnostic Scale (ISTCMDS)’

#### Exclusion criteria

Patients with any of the following conditions will be excluded:
A.Intracerebral haemorrhage or subarachnoid haemorrhage confirmed by computed tomography or magnetic resonance imagingB.Recurrent stroke with a neurofunctional disability that can affect the results of this studyC.A history of a brain tumour, traumatic brain injury, haematopathy, etc.D.Other severe diseases that can affect cerebral infarction therapy outcomes and mental impairmentE.A pregnant or lactating statusF.Participation in another clinical trial for a drug, acupuncture or rehabilitationG.Skin lesions and other skin diseases at acupuncture points

### Who will take informed consent? {26a}

Consent will be obtained by one of the researchers in the presence of a witness. After providing written informed consent, eligible patients will be asked to complete a general information form including their name, sex, age and medical history and complete the same day scale as the baseline assessment. A researcher who is a neurologist with more than 5 years of experience will evaluate the NIHSS, Simplified Fugl-Meyer assessment scale (FMA), modified Ashworth scale (MAS) and Barthel Index (BI) scores for each participant. These scores will be used to determine the eligibility of a patient for the study in accordance with the inclusion and exclusion criteria. The personal information of potential as well as enrolled participants will be collected and stored confidentially.

### Additional consent provisions for collection and use of participant data and biological specimens {26b}

On the consent form, the participants will be asked whether they permit the continued use of their data in case of withdrawal from the trial. The participants will also be asked for permission to share relevant data with the research team from the universities taking part in the study or with regulatory authorities, when relevant. This trial does not require the collection of biological specimens for storage.

## Interventions

### Explanation for the choice of comparators {6b}

In China, stroke patients are often treated with acupuncture. Thus, the patients can easily determine whether fake acupuncture is used. Therefore, we decided to perform standard procedure acupuncture rather than sham acupuncture for the control group.

### Intervention description {11a}

#### ‘Hand and foot acupuncture with twelve needles’ group

‘Hand and foot acupuncture with twelve needles’ involves 12 acupoints, including hegu (LI4, bilateral), neiguan (PC6, bilateral), quchi (LI11, bilateral), zusanli (ST36, bilateral), yanglingquan (GB34, bilateral) and sanyinjiao (SP6, bilateral).The patient will be asked to rest in a supine position, and the skin at the acupoints will be disinfected routinely. Disposable acupuncture needles will be inserted into the abovementioned acupoints (15–20 mm deep). After twirling, these needles will be left in place for 20 min. The procedure will be repeated five times per week for 4 weeks.

### Routine acupuncture group

(3)Routine acupuncture [26] will be performed in accordance with the Evidence-based Guidelines of Clinical Practice in Chinese Medicine Internal Medicine, and needles will be placed at neiguan (PC6), shuigou (DU26), sanyinjiao (SP6), jiquan (HT1), chize (LU5), weizhong (BL40), jianyu (LI15), shousanli (LI10), hegu (LI4), huantiao (GB30), yanglingquan (GB34), xuanzhong (GB39) and taichong (LR3) on the hemiplegic side.(4)The patient will be asked to rest in a supine position, and the skin at the acupoints will be disinfected routinely. Disposable acupuncture needles will be inserted into the above acupoints at a depth of 15–20 mm, except at huantiao where the needle will be inserted 30 mm deep. After twirling, these needles will be left in place for 20 min. The procedure will be repeated five times per week for 4 weeks.

### Criteria for discontinuing or modifying allocated interventions {11b}

There will be no special criteria for discontinuing or modifying the allocated interventions.

### Strategies to improve adherence to interventions {11c}

Patients will be followed up via telephone calls or by outpatient follow-up systems. We also plan to hold awareness meetups regularly to encourage patient involvement. All assessments will be performed at baseline (on the day of enrolment) and 2 weeks, 1 month, 2 months and 3 months after enrolment (follow-ups).

### Relevant concomitant care permitted or prohibited during the trial {11d}

#### Routine interventions

Symptomatic treatment according to the 2010 Guidelines of Chinese Stroke Prevention and Control includes the prevention and treatment of complications, glycaemic control and blood pressure control.Rehabilitation training includes physical therapy (PT) and occupational therapy (OT) for 5 days per week.Acupuncture will be performed in accordance with the Standards for Reporting Interventions in Clinical Trials of Acupuncture (STRICTA) guidelines, after the participant’s condition is stabilised by TCM practitioners (trained medical acupuncturists) using routinely disinfected disposable acupuncture needles (size 0.30 × 40 mm, Suzhou Dongbang Medical Apparatus Co., Ltd., Suzhou, China).

### Provisions for post-trial care {30}

There is no anticipated harm associated with or compensation for trial participation.

### Outcomes {12}

#### Primary outcome measure

The simplified FMA [27] will be used to estimate the capacity of autonomous movement of the limb and includes items on reflex activity, flexor synergy, extensor synergy, wrist and hand, coordination and speed. The total score possible is 100 points, and motor function of the upper limbs (33 items, 66 points) and lower limbs (17 items, 34 points) will be assessed.

#### Secondary outcome measures

The NIHSS [28] will be used to assess the neurological deficits related to stroke and includes items on consciousness, language, movement, sensation, ataxia, eye movement, visual field and others. The scores range from 0 to 42, with higher scores indicating more severe neurological deficit.

The MAS [29] is a grading standard used to measure muscle tone with a scale ranging from 0 to 4 points.

The BI [30] will be used to determine the functional status of patients’ daily activities, which includes bowel control, feeding, dressing, access to the toilet, grooming, bathing, climbing from a wheelchair to bed and back to a wheelchair, walking 45 m on a horizontal surface and going up and down the stairs. The scores range from 0 to 100.

### Participant timeline {13}

All patients will be assessed by a researcher using the above scales on the day of enrolment and 2 weeks, 1 month, 2 months and 3 months after enrolment.

### Sample size {14}

The primary efficacy parameter is the change in the FMA score from baseline to 3 months after the treatment [31]. According to our preliminary test and a previous study, the primary efficacy parameter (FMA score) of the control group (rehabilitation treatment) will increase by 12.11 points and that of the treatment group (scalp acupuncture combination rehabilitation treatment) will increase by 25.82 points. The FMA average standard deviation is expected to be approximately 4. Considering a one-sided 5% significance level, 80% power and the above data (*μ*_1_ = 25.82, *μ*_2_ = 12.11, *σ* = 4, *α* = 0.025, 1–*β* = 0.8), according to NCSS-PASS V20.0.3 software (https://www.ncss.com/software/pass/), approximately 86 participants will be required in each group to achieve a sufficient sample size. Accounting for a dropout rate of 20%, each group must include 104 initial participants. Therefore, we plan to include a total of 208 participants divided equally into two groups.

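### The 86 per group does not follow from the printed sample-size inputs, which give 3, and those inputs describe a different comparison, so power for the trial's own contrast cannot be derived

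*Protocol article*

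**What the plan says.** The Sample size section {14} of the protocol article defines the endpoint: "The primary efficacy parameter is the change in the FMA score from baseline to 3 months after the treatment". It then gives the planning values. The "control group (rehabilitation treatment) will increase by 12.11 points", and the "treatment group (scalp acupuncture combination rehabilitation treatment) will increase by 25.82 points". On spread it says: "The FMA average standard deviation is expected to be approximately 4". The error rates are introduced with "Considering a one-sided 5% significance level, 80% power and the above data", but the parameter list that follows gives alpha as 0.025. From these inputs, with PASS named as the software, it concludes that "approximately 86 participants will be required in each group to achieve a sufficient sample size". A 20% dropout allowance raises this to 104 per group, 208 in total.

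The Objectives section {7} describes another comparison: the twelve-needle technique is to be compared "with that of routine acupuncture technique in hemiplegia patients". The abstract's Methods paragraph puts both groups on conventional rehabilitation. The section on the choice of comparators {6b} explains that the control was deliberately made real acupuncture and not sham. The Trial design section {8} calls the trial a superiority trial and gives no margin. The Statistical methods section {20a} plans ordinary t or rank-sum comparisons between groups.

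**The concern.** Two things look wrong, and they are separate.

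First, a difference of 13.71 points against an SD of 4 is about 3.4 standard deviations. An effect of that size needs a handful of patients, so 86 per group cannot be the software's answer to the printed inputs.

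Second, the difference belongs to acupuncture added to rehabilitation against rehabilitation without it. It does not estimate the difference between two acupuncture schemes when both arms also receive rehabilitation, and the article gives no expected difference for that contrast.

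At stake is the only justification offered for enrolling 208 people and for the 80% power statement on the primary outcome. As it stands, a reader cannot tell what difference between the two acupuncture arms the trial was built to detect.

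**Working it through.** **Inputs (Sample size {14}).** Means 25.82 and 12.11; SD 4; power 0.80; alpha 0.025 in the parameter list, one-sided 5% in the sentence. Allocation is 1:1 (Trial design {8}).

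Difference = 25.82 − 12.11 = 13.71. Standardised difference d = 13.71/4 = 3.43.

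**Step 1: try to reproduce 86.** Normal approximation at one-sided 0.025:

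n = 2 × [(1.960 + 0.842) × 4 / 13.71]² = 1.3, so 2 per group.

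The t test (noncentral t, 2n − 2 degrees of freedom) is the better guide at such small n:

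| Reading of alpha | Power, n = 3 | Power, n = 4 | n needed |
|---|---|---|---|
| one-sided 0.05 | 96.0% | 99.5% | 3 |
| one-sided 0.025 | 87.4% | 97.9% | 3 |
| two-sided 0.05 | 87.4% | 97.9% | 3 |
| two-sided 0.025 | 72.7% | 93.5% | 4 |

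The figure of 86 is not reproduced. It is about 29 times the 3 that the inputs require (86/3 = 28.7). With 86 per group, power for the stated inputs is essentially 100%.

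**Step 2: what would give 86?** Normal approximation, one-sided 0.025, 80% power:

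- Keeping the difference: SD = 13.71 / [2.802 × √(2/86)] = about 32, against a stated 4.
- Keeping the SD: difference = 2.802 × 4 × √(2/86) = 1.71 points, against a stated 13.71.
- With a superiority margin of 12 points: 13.71 − 12 = 1.71, and n = 2 × (2.802 × 4 / 1.71)² = 85.9. The article mentions no margin, so this is conjecture.

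**Step 3: compare the contrasts.**

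| | Planning values | This trial |
|---|---|---|
| Experimental arm | scalp acupuncture + rehabilitation | twelve-needle acupuncture + rehabilitation |
| Control arm | rehabilitation | routine acupuncture + rehabilitation |

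The control arms differ in whether acupuncture is given at all, and the experimental arms differ in technique.

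**Step 4: the dropout step.** To keep 86 after a 20% loss requires 86/0.8 = 107.5, so 108. The stated 104 is 86 × 1.2 = 103.2, rounded up. From 104, a 20% loss leaves 104 × 0.8 = 83.2, or 83 per group.

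**Step 5: what 208 participants can detect.** By t test with 83 per group, 80% power and two-sided 5% (equivalently one-sided 2.5%), the detectable difference is 0.437 SD:

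| SD of change | Detectable difference |
|---|---|
| 4 (as stated) | 1.75 points |
| 8 (assumed) | 3.5 points |
| 12 (assumed) | 5.2 points |

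The figure is 0.43 SD if 86 per group are analysed. It is 0.39 SD (1.56 points at SD 4) if all 104 are analysed, as filling gaps with the last measurement {20c} might allow.

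**The case against.** **The trial is larger than its inputs require, so no harm follows.** The first half is right, and it matters. A reader might infer from the failed arithmetic that the trial is underpowered. The document does not support that: for a 13.71-point difference at SD 4, 86 per group is far more than enough. What remains is that 13.71 is not an effect for this contrast, so the surplus gives no assurance about it.

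**A null result would still be informative.** A reader might also fear that a null result would be wrongly taken to exclude a 13.71-point benefit. That does not hold. With 83 to 86 per group the 95% confidence interval has a half-width of about 1.2 points at SD 4 and about 3.7 at SD 12 (83 per group), and stays under 10 points even at SD 32. A result centred near zero would properly exclude 13.71.

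**A margin may have been entered and left to the full protocol.** This is possible, and a 12-point margin comes very close. But the match needs the normal approximation and one-sided 0.025. By t test, 86 gives 79.6% power and 87 are needed; at one-sided 5% the same margin gives 68. The printed parameter list also reads as complete. It would be tempting to conclude that the trial was sized for one hypothesis and will test another, but without a stated margin that is only a possibility, and the point does not rest on it.

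**The inputs also draw on a preliminary test.** The section credits its own preliminary test as well as a previous study, and does not describe the preliminary test's arms separately. The labels attached to the two means are still those of the other comparison.

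**An article condenses the protocol.** That would excuse a missing calculation. This one is printed with its inputs and its answer, and the two disagree.

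**Conclusion.** The point stands on both counts. The printed inputs need 3 per group, and no more than 4 under any reading of alpha, so 86 is not their result. The planning difference is labelled as coming from a comparison that this trial does not make. The size of the trial is not shown to be wrong. Its stated derivation is, and power for twelve-needle against routine acupuncture cannot be worked out from the document because no expected difference for that contrast is given. How 86 arose is unknown.

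The arithmetic assumes a two-sample t test on change scores with equal groups and a common SD. The detectable differences assume 83 analysed per group and two-sided 5%. Only the SD of 4 comes from the article; 8 and 12 are illustrative.

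**What to change.** Keep 208 participants and rewrite the Sample size section:

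1. Remove the 13.71-point difference as the planning effect.
2. Resolve the conflict between one-sided 5% and alpha 0.025, and state one level and sidedness. The figures below are for two-sided 5% (one-sided 2.5%); at one-sided 5% they would be smaller.
3. State the detectable difference for the number expected to be analysed. With 104 randomised per group and 20% dropout, 83 remain, giving 80% power for about 0.44 SD: 1.75 points at SD 4, and 3.5 and 5.2 points at assumed SDs of 8 and 12.
4. Correct the dropout step. Retaining 86 would need 108 per group, so either describe 104 as leaving 83 or stop presenting 86 as the number retained.
5. If a superiority margin was entered in the software, state it and test against it. Otherwise say that the test is against zero difference.

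The cost is rewording, with no extra patients. The stated target becomes a standardised detectable difference and no longer an expected effect, which is as much as the available information supports.

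### The 20% dropout allowance is computed as 86 × 1.2 rather than 86 / 0.8, so 104 per group covers about 17% dropout, not 20% (minor)

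*Protocol article*

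**What the plan says.** Everything needed is in the protocol article under Sample size {14}. The section states the requirement before dropout: "approximately 86 participants will be required in each group to achieve a sufficient sample size". It then adds the allowance: "Accounting for a dropout rate of 20%, each group must include 104 initial participants". From this it concludes: "we plan to include a total of 208 participants divided equally into two groups".

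The article gives no other dropout rate and no other inflation rule. The section on missing data {20c} says that a missing value will be replaced by the last one measured.

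**The concern.** A dropout rate is a share of the people who start. The sentence is framed that way, since it moves from a required number to a number of initial participants. To end with n after losing a fraction d, one enrols n / (1 − d). Multiplying by (1 + d) takes the 20% of the smaller number and always falls short.

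What is at stake is the published reason for enrolling 208 people. A reader will take it that the trial can lose one participant in five and still keep the number it says it needs, and that is not so. The same rule would also under-inflate any new base number if the calculation is redone.

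**Working it through.** **Inputs**, all from Sample size {14}: required number per group n = 86; dropout d = 0.20; enrolled per group 104; total 208.

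**Reproducing the plan's figure.** n × (1 + d) = 86 × 1.2 = 103.2, rounded up to 104, and 2 × 104 = 208. Both stated figures are matched exactly.

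**The figure that keeps 86 after 20% loss.** n / (1 − d) = 86 / 0.8 = 107.5, rounded up to 108, and 2 × 108 = 216. The plan is 4 per group, or 8 in total, below this.

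**What 104 delivers.**
- Completing at 20% dropout: 104 × 0.8 = 83.2, about 83 per group, against 86.
- Largest dropout that still leaves 86: 1 − 86/104 = 18/104 = 17.3%.

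**Whether the word approximately absorbs the gap.** Values that round to 86 run from 85.5 to 86.5. Dividing by 0.8 gives 106.9 to 108.1, so 107 to 109 per group. For 104 to be enough, the requirement would have to be 83.2 or less.

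**Size in terms of power, conditional on 86 giving exactly 80%** (normal approximation, two groups of equal size):
- Two-sided 5%, which is the same as one-sided 2.5%: standardised difference = (1.960 + 0.842) × √(2/86) = 0.427. At 83 per group, 0.427 × √(83/2) − 1.960 = 0.79, so power is 78.6%.
- One-sided 5%: standardised difference = (1.645 + 0.842) × √(2/86) = 0.379. At 83 per group, 0.379 × √(83/2) − 1.645 = 0.80, so power is 78.8%.

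Both levels are shown because the section names a one-sided 5% level in words and α = 0.025 in the bracketed inputs.

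**Whether that condition holds.** The printed gains are 25.82 and 12.11 with a standard deviation of 4. The difference is 13.71 and the standardised difference is 13.71/4 = 3.43. At two-sided 5%, n = 2 × (1.960 + 0.842)² × 4² / 13.71² = 1.3, so 2 per group; a t-test calculation gives 3, or 4 at two-sided 2.5%. For 86 per group to be the 80% requirement at a difference of 13.71, the standard deviation would have to be about 32 (two-sided 5%) or 36 (one-sided 5%). On the printed inputs, power is essentially 100% at either 83 or 86 per group.

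**The case against.** **The gap is trivial.** It is 3 completers per group, the 20% is itself a planning guess, and 104 covers any dropout up to 17.3%. This stands as an argument on severity. It does not make the sentence correct.

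**Multiplying by 1.2 is common practice.** It may be, but enrolling 104 and losing 20% of them still leaves 83.

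**Dropouts stay in the analysis.** With the last value carried forward under {20c}, participants who leave may still be analysed, so the number analysed could be nearer 104 than 83. This stands in part: 83 is the number expected to complete, and should not be presented as the number analysed. It does not repair the inflation step, whose stated purpose is to allow for dropout.

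**The base number is unsound anyway.** This is true and is the larger problem in the section. A reader might infer from the shortfall that the trial has only 78.6% power, or that it misses its 80% target. The document does not support that. The standardised difference of 0.43 behind the 78.6% is back-solved from 86 and appears nowhere in the plan, while the printed inputs give nearly 100%. What is shown is only that 83 is fewer than the 86 the plan says it needs.

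**Conclusion.** The inflation step is wrong as written: 104 per group does not preserve 86 at 20% dropout. The correct figure from the plan's own two numbers is 108 per group (216 in total), and 104 covers at most 17.3%. This rests only on 86, 20% and 104 as printed, and on reading dropout as a share of those enrolled.

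The severity is minor. The deficit is about 3 completers per group. The associated loss of about 1.2 to 1.4 percentage points of power holds only if 86 truly is the 80% requirement, which the printed means and standard deviation do not support. It would also be wrong to infer that more participants must be recruited, since an accurate statement of what 104 covers is enough.

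**What to change.** Correct one sentence in Sample size {14} and leave enrolment at 208. Either form below would do:
- 104 per group (208 in total) allows for about 17% dropout while keeping 86 per group; or
- at 20% dropout, about 83 of the 104 enrolled per group are expected to complete.

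If the sponsor prefers to keep the claim that 20% is allowed for, the matching number is 108 per group, 216 in total.

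Do not add 78.6% or any other revised power figure. Beside inputs that imply nearly 100%, it would create a new contradiction. Re-derive the base number separately, with one consistent significance level, and then inflate the result as n / (1 − 0.20).

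The cost of the wording change is one sentence and a slightly less favourable stated dropout tolerance. Only the option of 108 per group adds participants, 8 in all.
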